**Method:**

For Phase I, a convenience sample of ~50 adolescents will be recruited. These participants will have their PAEE assessed in three different modes of commuting. Regarding phase II, a total of 300 adolescents from different schools in three Spanish cities will participate in this cluster randomized controlled trial. As many schools as necessary to meet the target sample will be included. In addition, each school will be randomized as either an intervention or control group. Participants from intervention schools will be asked to complete a school-based cycling intervention, while participants from control schools will be asked to continue their same habits for 8 weeks. The school-based cycling intervention will last for 8 weeks and will include *Bikeability* sessions, along with encouragement strategies to increase adherence to cycling to and from school.

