Therefore, this protocol describes the rationale and methodology of the ENERGY expenditure of school Commuting study (The ENERGYCO study). ENERGYCO project will address the gaps and limitations in the existing scientific literature regarding the PAEE that occurs during cycling to school. Considering the previous literature and existing gaps, the ENERGYCO project will be divided into two phases. Phase I will focus on using a portable metabolic system to assess PAEE associated with different modes of commuting (i.e., walking, cycling, motorized vehicles) under free-living conditions in Spanish adolescents. Additionally, Phase I will serve to develop a predictive equation that will be used in Phase II to measure PAEE associated with different modes of commuting to and from school. Additionally, considering the ongoing debate regarding the health benefits of ACS and the scarcity of studies examining the effects of school-based cycling interventions on RMR and PAEE, the Phase II will aim to assess the effects of a school-based cycling intervention on RMR and PAEE, as well as on other physiological (i.e., basal heart rate, blood pressure, and body temperature), physical (i.e., PA levels, anthropometric measures, body composition, physical fitness, and motor competence), and psychosocial outcomes (e.g., perceived barriers to active commute to school, self-esteem, and mental health) on Spanish adolescents. It is hypothesized that, in Phase I, using a portable metabolic system under free-living conditions will provide accurate and distinct measurements of PAEE associated with different commuting modes in Spanish adolescents. Specifically, we hypothesize that these measurements will highlight significant differences in PAEE across commuting modes, offering a more precise understanding of how commuting impacts adolescents’ physical activity levels. Additionally, we expect the data collected in Phase I to contribute to the development of a valid and reliable predictive equation for estimating PAEE during commuting to and from school. we hypothesize that a school-based cycling intervention will lead to a significant increase in both RMR and PAEE compared to a control group. We further hypothesize that the intervention will improve physiological outcomes (e.g., reductions in basal heart rate), physical outcomes (e.g., enhanced physical fitness and motor competence), and psychosocial outcomes (e.g., increased self-esteem) among Spanish adolescents.

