
**Table 1 tab1:** Schools’ inclusion and exclusion criteria.

Inclusion criteria	Exclusion criteria
The school has a specific space for parking bicycles and allows their parking	The school does not have specific infrastructure to park or store bicycles
The school has at least two classes per grade	The school offers bus transportation to the adolescents
At least eight students from the school will agree to participate in the study	The school is already participating in other interventions focused on promoting healthy behaviors
Schools from urban areas	The school has implemented an intervention to encourage commuting to school within the last year
	Schools from rural areas

**Table 2 tab2:** Participants’ inclusion and exclusion criteria.

Inclusion criteria	Exclusion criteria
Adolescents’ females and males aged from 12 to 17 years old (both ages included)	Adolescents younger than 12 years or older than 17 years
Healthy participants who can ride a bicycle safely and without difficulty.	Participants with any injury or medical condition that prevents safe participation in cycling to and from school
Be able to cycle to and from school at least 3 days per week during eight consecutive weeks (Intervention group)	Insufficient ability to ride a bicycle or inability to cycle to and from school at least 3 days a week (Intervention group)
Not to cycle to and from school more than 3 days a week during the last year	Participants who have cycled to and from school more than 3 days a week during the past year
To present a valid signed consent from their parents or legal guardians	Participants without a valid, signed parental or guardian consent form
To present valid data at baseline and follow-up from all the outcomes assessed	Participants who do not provide valid data for all assessed outcomes at baseline and follow-up

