### Description and rationale of the ENERGYCO study

2.5

In Phase I the PAEE of different modes of commuting will be quantified by analyzing each participant individually in different controlled environments. For phase II, after recruiting schools and participants, an eight-week school-based cycling intervention will be implemented. The choice of an eight-week duration was based on the results reported in the systematic review by Dorothea et al. (47) on the effects of cycling interventions in a school setting. For example, although interventions lasting longer than 8 weeks demonstrate positive changes in physical fitness (43, 48), they also exhibit lower adherence, with a higher dropout rate among participants post-intervention. Therefore, considering that interventions lasting 4 to 8 weeks show effects on self-efficacy (49) or PA levels (50) and report a lower dropout rate, an eight-week duration was chosen for the school-based cycling intervention. The intervention will consist of adolescents having to cycle to and school for eight consecutive weeks. To encourage participants to complete the intervention, they will take part in a *Bikeability* training and different encouragement strategies will also be used during this period. Moreover, the ENERGYCO school-based cycling intervention shows relevant factors described in the current National Education Law for the curriculum of Compulsory Secondary Education. This approach is based on strategies proposed by the Active Living by Design Community Action Model (51), which involves preparing through the development of interventions, promoting education, and motivating students to cycle anywhere, as well as organizing activities with incentives and programs to engage participants. Regarding the control groups, participants in these schools will be asked to continue their daily habits. In addition, at the end of the eight-week cycling intervention in schools, control schools will be given the opportunity to conduct the *Bikeability* sessions and will receive all the motivational strategies used for the participating adolescents.

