##### Mode of active commuting to school and related outcomes

2.7.2.14

ACS will be evaluated using the PACO questionnaire^3^, a reliable and valid tool for young Spaniards (Kappa ranged from 0.42 to 0.94) (86, 87). The PACO questionnaire consists of four self-report items designed to assess the usual mode of commuting and the weekly frequency of commuting among children and adolescents. The four questions include: (i) *“How do you usually get to school?”* (ii) *“How do you usually get home from school?”* (iii) *“How did you get to school each day?”* and (iv) *“How did you get home from school each day?”* Participants will select their mode of commuting from predefined options such as walking, cycling, car, motorcycle, bus, public bus, metro/train/tram, or other (requiring mode specification). The main variables of interest are the percentage of usual cycling and active modes of commuting to and from school, along with the weekly number of cycling and active trips. Additionally, participants will report their distance from school and the time it takes to commute from home to school. Response options for distance range from less than 0.5 km to 5 km or more, while response options for travel time range from less than 15 min to 60 min or more (86). Other factors associated with ACS, such as independent mobility, will also be analyzed as secondary variables. Data will be aggregated by participant and collected during baseline and follow-up assessments. Overall, these questionnaires provide valuable data on modes of commuting, frequency of active commuting, distance covered, and time spent during the commute for both adolescents.

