#### Statistical analysis

2.10.2

Descriptive analyses of all study variables presented with the mean (standard deviation) and frequencies (percentage) will be performed. Subsequently, the normality of the variables will be analyzed using histograms and normality tests. In Phase I, for the comparison of PAEE between the different modes of commuting (i.e., walking, cycling, and motorized-vehicle), a repeated measures ANOVA will be performed using the per-protocol approach. In addition, Student t-test or Mann–Whitney tests will be performed to compare the fluctuation of PAEE according to speed or distance commuted between active modes of commuting (i.e., walking vs. cycling).Within Phase II, the effects of the school-based cycling intervention on RMR and other health-related outcomes will be studied using an analysis of covariance (ANCOVA). Post-intervention RMR and other-health related values will be included as dependent variables, group (i.e., experimental group vs. control group) as fixed factor, and baseline outcome data as covariates. To evaluate the effect of the intervention on the secondary outcomes (i.e., physiological, physical, and psychosocial outcomes), we will conduct the same analysis used for the main outcomes (i.e., ANCOVA analysis using the intention-to-treat approach). Moreover, to control the variability between schools, the analyses will include adjustments for contextual and organizational variables, such as the SES of the school area, the length of cycling lanes, the availability of bicycle parking, and the level of engagement of teachers and students in the intervention. The estimates will be present as raw and standardized (z-scores; i.e., mean differences between follow-up and baseline data divided by the standard deviation), as an indication of the change the post-intervention z-scores will be calculated relative to the baseline mean and standard deviation. Effect sizes will be categorized as small (0.2 SDs), medium (0.5 SDs), and large (0.8 SDs), based on Cohen (93). Finally, to analyze the influence of covariates on the association between the intervention and the main outcomes (i.e., RMR and PAEE), mediation analyses will be performed. The intervention will be included as the independent variable, and the main outcomes as the dependent variables. Covariates included in the mediation analysis will encompass body composition, physical function, cognitive determinants, perceived barriers or autonomy, built-environment characteristics, weather, among others. In the statistical analysis, a value of *p* < 0.05 will be considered statistically significant.

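### Habitual walkers may enter both arms, yet the Phase II ANCOVA has one group effect and names no term for baseline commuting mode, so cycling versus walking is pooled with cycling versus passive travel

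*Protocol article*

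**What the plan says.** The comparator is usual behaviour. The Abstract states that "participants from control schools will be asked to continue their same habits for 8 weeks", and section 2.5 that "participants in these schools will be asked to continue their daily habits".

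The only participant criterion on commuting history is in Table 2: "Not to cycle to and from school more than 3 days a week during the last year" (with the matching exclusion). Walking is not mentioned. Table 1 takes urban schools only and excludes a school if "The school offers bus transportation to the adolescents".

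The Introduction hypothesises that "a school-based cycling intervention will lead to a significant increase in both RMR and PAEE compared to a control group". It also treats walking as an active mode that adds to physical activity, and says the difference between walking and cycling matters.

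Section 2.10.2 sets the effect model: follow-up value as the dependent variable, "group (i.e., experimental group vs. control group) as fixed factor, and baseline outcome data as covariates". To deal with differences between schools it adds contextual variables "such as the SES of the school area, the length of cycling lanes, the availability of bicycle parking" and school engagement. Neither this list nor the list of covariates for the mediation analysis names baseline commuting mode.

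The variable is available. Section 2.7.2.14 uses PACO to "assess the usual mode of commuting and the weekly frequency of commuting among children and adolescents", at baseline and follow-up. Section 2.4.1 places randomisation after the baseline assessment, so baseline mode is recorded before allocation.

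**The concern.** One group effect covers two different changes. A pupil who used to be driven replaces a passive trip with an active one. A pupil who used to walk replaces one active trip with another, usually a shorter one in time. The plan's own Phase I exists because these modes are expected to differ in energy cost, but the Phase II model does not carry the distinction forward.

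What is at stake is interpretation. A small or null group effect could mean that cycling to school does little, or that a good part of the intervention arm gave up walking. As the model stands, the two could not be told apart. A difference between arms in the share of walkers, which can arise because whole schools are randomised, would also move the estimate to the extent that the baseline outcome does not already account for it.

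**Working it through.** **The plan's own figure.** Section 2.4.2 gives 250 evaluable participants for effect size f = 0.25, alpha 0.05 and power 95%. A noncentral F calculation gives 251 with two numerator degrees of freedom and 210 with one, the case for two groups. At N = 250 with one degree of freedom, power is 97.6%. The effect size is stated for the two-group comparison and is not divided by baseline mode, so it says nothing about walkers and is not used further here.

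**What the single group effect estimates.** Let w be the share of baseline walkers (similar in both arms), D_p the effect in passive commuters and k·D_p the effect in walkers. Then

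pooled effect = (1 − w)·D_p + w·k·D_p = D_p·[(1 − w) + k·w].

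The documents give neither w nor k. Over assumed ranges, the pooled effect as a fraction of D_p is:

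| w (assumed) | k = 0.5 | k = 0 | k = −0.5 |
|---|---|---|---|
| 20% | 0.90 | 0.80 | 0.70 |
| 40% | 0.80 | 0.60 | 0.40 |
| 60% | 0.70 | 0.40 | 0.10 |

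**Can k be zero or negative for commute energy?** On one route, energy is rate × time, so

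cycled/walked energy = r × (walking speed / cycling speed),

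where r is the per-minute cost of cycling relative to walking. The route length cancels. With the speeds in section 2.6.1 (4.4–4.6 km/h and about 15 km/h), break-even is r = 15/4.6 = 3.26 to 15/4.4 = 3.41. At 4.5 km/h, assumed values of r give:
- r = 1.5: 0.45
- r = 2.5: 0.75
- r = 3: 0.90
- r = 4: 1.20

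So the sign for a walker is open. These speeds were chosen to plan the Phase I simulations (15 km/h belongs to a 4,200 m cycling route) and do not describe Phase II trips. The calculation shows a possibility only.

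**Which outcomes it reaches.**
- *MVPA* (accelerometer, seven days): walking and cycling both belong to the pupil's day, so lost walking can offset gained cycling.
- *PAEE*: this depends on the definition. Section 2.7.1.2 describes Phase II PAEE over cycling trips during the intervention, so energy no longer spent walking is never counted. The Introduction and section 2.7.2.18 speak of PAEE for different commuting modes, and the Discussion of daily PAEE; there it could be counted.
- *RMR*: trip energy says nothing direct about resting metabolism. Dilution is plausible.

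**Precision of a group-by-mode term.** In SD units with equal arms, SE = √[4/(N·w) + 4/(N·(1 − w))]. With N = 250 and an assumed w = 30%, SE = √(4/75 + 4/175) = √(0.0533 + 0.0229) = 0.276. A difference of 0.5 SD between strata gives z = 0.5/0.276 = 1.81, or about 44% power before any allowance for clustering.

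**The case against.** The strongest reply is that usual behaviour is a legitimate comparator and is the one stated, so cycling versus the usual mix is simply the trial's question. That stands, and the overall contrast need not be replaced. It does not remove the difficulty of explaining a small effect when the mix goes unreported.

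Next, the baseline outcome is already a covariate and the adjustment list is open-ended. For activity outcomes, the baseline value will carry part of a walker's higher activity. This stands in part, but a baseline covariate cannot represent a different treatment effect.

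A further reply is that subgroup and interaction terms usually belong in an analysis plan, which is not shown. Their bare absence would not be a finding. Here the article fixes the effect model and names its adjustments, and the point concerns that stated choice.

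Three stronger readings are tempting and are not supported:
- A reader might infer a definite loss of power by applying the planned effect size to passive commuters alone. Section 2.4.2 states it for the comparison of the two groups as recruited, and the walker share and effect are not given.
- A reader might infer that the hypothesised rise in RMR would be reversed. The trip-energy argument does not extend to RMR.
- A reader might infer that walkers predominate, or that few schools make imbalance likely. Car, motorcycle, public bus and metro remain among the PACO options, the article says as many schools as needed will be recruited, and 1:1 allocation within city limits imbalance between cities.

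**Conclusion.** The point holds in a limited form. The documents admit habitual walkers to both arms, pool them with passive commuters under one group effect, and do not name a baseline variable that they already collect. The likely consequence is dilution. For outcomes that count all activity (MVPA, and daily PAEE if walking is included), partial offsetting is also possible. How much cannot be derived from the documents: it depends on the share of walkers and the effect in them, and the table of fractions rests on assumed values of both. This is mainly a question of interpretation. It does not show bias, since randomisation balances walkers on average, and it does not show that the stated sample size is inadequate. The change is worth making because it is cheap and improves what the trial can conclude.

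**What to change.** 1. In section 2.10.2, add baseline usual commuting mode from PACO (walking versus passive, with a stated rule for occasional cyclists) as a covariate in every Phase II effect model. This deals with chance imbalance and may improve precision. Alone it does not separate the two contrasts.
2. Pre-specify a group-by-baseline-mode term as a secondary analysis, and report the effect separately for baseline walkers and passive commuters, with the share of each by arm. Label it supportive, because it is likely to be underpowered.
3. Word the overall conclusion as cycling versus the usual mix of modes. The hypothesis need not be restated for passive commuters; that would change the trial's question.
4. Reconcile section 2.7.1.2 with the Introduction, section 2.7.2.18 and the Discussion, so that Phase II PAEE has one definition and walking energy is counted in both arms.

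Items 1 to 3 need wording only, since the variable is already collected in both arms at baseline. They use one to three degrees of freedom, and the stratum estimates will be less precise than the pooled one. Item 4 needs a decision on the outcome definition; section 2.7.2.18 already plans GPS and accelerometer data at baseline and follow-up that could support it.

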### Study design and participants

2.1

The ENERGYCO study is a cluster randomized controlled trial to be conducted in high schools from three Spanish cities (Granada, Jaén, and Almería), where the schools will be the units of randomization, and individuals within the schools will be the units of analysis (participants). This project will consist of two main phases: Phase I will present a cross-sectional design which will take place before starting the Phase II. A cross-sectional approach will be adopted due to its suitability for capturing a snapshot of key variables of interest at a specific point in time, aligning with the objectives of this phase (i.e., comparing PAEE associated with different modes of commuting to school and developing predictive equations for measuring PAEE in Phase II). In contrast, for Phase II a cluster parallel-arm design will be employed to allocate interventions effectively to larger groups while accounting for potential intra-cluster variability, enhancing the external validity and generalizability of the results. The ENERGYCO study has been approved by the Review Committee for Research Involving Human Subjects at the University of Granada (Reference: 2496/CEIH/2021) and registered with a ClinicalTrials.gov ID: NCT06414668. In addition, the present study protocol has been written in accordance with the Standard Protocol Items: Recommendations for Interventional Trials (SPIRIT) statement (See Supplementary material 1).

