#### School recruitment and randomization

2.4.1

In Phase I, a convenience sample of approximately 50 students will be recruited. A call to action will be used to engage adolescents through the development of infographics and information about the aims of this phase, which will be disseminated through social media, personal contacts, or emails. Since these tests will be conducted outside the school timetable, no schools will be directly contacted. Instead, parents or legal guardians will be responsible for contacting the research team if their children are interested in participating in the study and they provide their consent. In this call to action, incentives, such as activity wristbands will be given away to participating adolescents. For Phase II, a specific selection protocol will be implemented through a random draw. A list of all public secondary schools in each of the participating cities of the government educational institutions in Andalucía will be obtained. The schools in the three cities (Granada, Almería, Jaén) will be contacted by phone, and if they are interested in participating, they will have to meet a series of inclusion and exclusion criteria presented in Table 1. During the call, a meeting will be arranged with interested schools to explain to the management team and teaching staff the main objective of the study, as well as to obtain official consent to participate in the project from the school. After that, the research staff with the help of Physical Education teachers will recruit participants and their families, by visiting selected classes and explaining the study to prospective adolescent participants and finally requesting the family’s consent. The inclusion and exclusion criteria for the participants are presented in Table 2. To complete the sample of students in the intervention group, several schools may be needed, as not all students will be able to participate in the school-based cycling intervention due to family reasons, distance, predisposition, etc. To encourage as many students as possible from the intervention school to participate (with their families’ consent) in the school-based cycling intervention, an incentive system will be planned similar to other studies (42, 43). This incentive will consist of a voucher to be redeemed for sports equipment, provided that the participant has completed the 8 weeks of intervention and presents valid data at both baseline and follow-up. Once finished the baseline assessment, the participating schools will be randomly assigned through a draw to either a control or experimental group.

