#### Sample size calculations

2.4.2

For Phase II, at least 250 participants are needed to ensure an acceptable sample size, assuming 5% precision (*α* err prob) and a very high statistical power of 95%. (Error 1-*β* err prob) (44). This calculation has been made considering a study objective where the effect of the intervention program on the different health variables of young people is evaluated (e.g., RMR, EE, PA levels, body composition, muscle strength). In this study there will be two main comparison groups (experimental group and control group) and for this the ANCOVA statistical analysis will be performed: fixed effects, main effects, and interactions (F test) and with an effect size = 0.25. It is assumed that there will be dropouts during the school-based cycling intervention (≈15% in the experimental group), so ≈300 adolescents will be recruited from different schools in the three Spanish cities. Following the forecasts in Figure 1, 100 adolescents would be needed in each city. The groups randomization will be done at a 1:1 ratio at city level (i.e., from each city, 50 participants will be randomized to intervention and 50 to control groups), as other studies have done before (45). Nevertheless, due to the low prevalence of cycling to school in Spain (46), we will try to recruit as many schools as necessary in each city to reach the number of 100 adolescents.

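### Schools are randomised, but the Phase II ANCOVA has no school term, so its standard errors are too small and the 5% error rate is not held

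*Protocol article*

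**What the plan says.** Section 2.1 of the protocol article states that "the schools will be the units of randomization, and individuals within the schools will be the units of analysis (participants"). Section 2.4.1 confirms that allocation is by school: after baseline, "the participating schools will be randomly assigned through a draw to either a control or experimental group". Section 2.4.2 adds that "The groups randomization will be done at a 1:1 ratio at city level", so city is the stratum.

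Section 2.10.2 gives the Phase II model. The post-intervention value is the dependent variable, with "group (i.e., experimental group vs. control group) as fixed factor, and baseline outcome data as covariates". Secondary outcomes get the same analysis as the main outcomes. On differences between schools, the section says that "to control the variability between schools, the analyses will include adjustments for contextual and organizational variables", and lists the socioeconomic status of the school area, cycling-lane length, bicycle parking, and teacher and student engagement in the intervention.

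Section 2.1 describes the cluster design as "while accounting for potential intra-cluster variability". Neither the analysis section nor the sample size section names a method that does this.

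**The concern.** When schools are randomised, the comparison between arms is a comparison between two sets of schools. Pupils in one school share influences, and the protocol describes several: Bikeability is taught at the school with its own Physical Education teacher (2.8), the weekly challenges are a points competition between schools (2.8), weather comes from the station nearest each school (2.7.2.19), and school engagement is expected to affect the intervention's effect (2.7.2.20). A positive within-school correlation is therefore to be expected.

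A single-level ANCOVA takes its error variance from variation between pupils and its degrees of freedom from the number of pupils. It ignores the school component of the variance of the group difference. A chance difference between a few schools could then be reported as an effect of cycling on resting metabolic rate (RMR), or on any other outcome analysed this way.

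This is not a detail left to an unseen analysis plan. The article states the model, its terms and its own remedy for between-school variability, and the remedy does not work.

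**Working it through.** **The plan's own figure.** Section 2.4.2 asks for at least 250 participants from an ANCOVA F test with alpha 0.05, power 95% and effect size 0.25 (read as Cohen's f, noncentrality N × f²). With numerator df = 2 this gives N = 251, which reproduces the 250. With df = 1, the value for a two-group main effect, it gives N = 210. Allowing 15% dropout, 250 / 0.85 = 295, close to the 300 to be recruited. Neither calculation contains a design effect, so the sample size, like the analysis, treats pupils as independent.

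**Inputs for the error rate.**
- Nominal two-sided alpha 5% and about 250 analysed (2.4.2).
- Whole-school allocation (2.1, 2.4.1).
- Model: group plus baseline (2.10.2).
- Assumed, because not given: ICC of the baseline-adjusted outcome 0.02, 0.05 or 0.10, and 6 to 30 schools. Six schools is one per arm in each of three cities. Thirty schools of 8 matches the minimum of eight pupils in Table 1.

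**Formula.** With m pupils per school, the variance of the group difference is understated by DE = 1 + (m − 1) × ICC, and the standard error by √DE. The true type I error of a nominal 5% test is about 2 × [1 − Φ(1.96 / √DE)].

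**Example**, 12 schools of 21 at ICC 0.05: DE = 1 + 20 × 0.05 = 2.00; √DE = 1.41; 1.96 / 1.41 = 1.39; true error = 16.6%.

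| Schools × pupils | DE at ICC 0.02 / 0.05 / 0.10 | Formula | Simulated ANCOVA |
|---|---|---|---|
| 6 × 42 | 1.82 / 3.05 / 5.10 | 14.6 / 26.2 / 38.5% | 14 / 27 / 39% |
| 12 × 21 | 1.40 / 2.00 / 3.00 | 9.8 / 16.6 / 25.8% | 9 / 17 / 27% |
| 18 × 14 | 1.26 / 1.65 / 2.30 | 8.1 / 12.7 / 19.6% | 8 / 12 / 19% |
| 30 × 8 | 1.14 / 1.35 / 1.70 | 6.6 / 9.2 / 13.3% | 7 / 9 / 14% |

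The simulations (at least 4,000 null trials per cell) fit ordinary least squares with group and baseline and test on individual-level degrees of freedom. At ICC 0 they return 4.2% to 5.4%, so the excess comes from the clustering alone.

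**Does the covariate adjustment repair it?** Four school-level covariates were added.
- Explaining none of the between-school variance, 12 × 21, ICC 0.05: 17.7%.
- Explaining half of it, ICC 0.05 / 0.10: 11.7% / 17.3% (12 × 21), 8.5% / 12.7% (18 × 14), 7.8% / 8.6% (30 × 8).

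The adjustment reduces the inflation at best. With six schools, intercept, group and four school-level covariates are six parameters for six schools, so no between-school information is left for error; a fifth covariate makes the group effect inestimable. Bicycle parking is a school inclusion criterion in Table 1 and should vary little.

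**Does a school-level analysis hold the level?** In the same simulations, baseline-adjusted school means regressed on group and city, with degrees of freedom equal to schools minus 4, rejected in 4.6% to 5.6% of null trials in every cell.

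**The case against.** The strongest reply is that the plan does adjust for school characteristics, that it may enrol many small schools, and that no ICC is given, so the largest figures show only the unfavourable end. This partly stands. The number of schools is open, the smallest clusters give milder inflation (5.8% for 8 per school at ICC 0.01), informative covariates lower it further, and at a residual ICC of exactly zero there is none. The size is therefore uncertain. The direction is not: no positive residual ICC leaves the test at 5%, and nothing in the plan makes zero plausible.

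Three narrower points also stand:
- Omitting city does not cause the inflation. Leaving out a balanced stratification factor usually makes standard errors too large. City belongs in the model because it is the allocation stratum.
- Section 2.7.1.2 defines Phase II physical activity energy expenditure (PAEE) from cycling trips during the intervention, so it is unclear how a baseline-adjusted ANCOVA applies to it. The point reaches PAEE to the extent that this model is used.
- A correct analysis costs power, so the change has consequences beyond wording. These are set out with the fix.

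**Conclusion.** The concern holds. The protocol fixes an individual-level analysis for a school-randomised trial, and its stated control for between-school variability does not restore valid standard errors. For about 250 analysed and an ICC of 0.02 to 0.10, the true type I error at nominal 5% is roughly 14% to 39% with 6 schools, 9% to 27% with 12, 8% to 19% with 18 and 7% to 14% with 30, before any help from covariates. If the covariates explain half of the between-school variance, about 8% to 12% remains at ICC 0.05 across 12 to 30 schools. These figures rest on assumed ICCs, assumed numbers of equal-sized schools and normal outcomes. The existence of the error rests only on a positive residual ICC. It affects the main test of the trial and must be corrected before analysis.

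**What to change.** In section 2.10.2, replace the Phase II ANCOVA by a linear mixed model: follow-up value on group, baseline value and city, with a random intercept for school and Kenward-Roger or Satterthwaite degrees of freedom. State in advance the number of schools below which the primary analysis becomes a comparison of baseline-adjusted school means, so that the method is not chosen after results are seen. Report the ICC for each main outcome.

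Remove the statement that covariates control the variability between schools. Any school covariates that are kept should be few, measured before allocation and named. Engagement in the intervention arises after randomisation and should not be in the primary model.

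**Cost.** Recruitment, conduct and data collection need not change for the analysis to be valid. Intervals will be wider. At the plan's effect (f = 0.25, that is d = 0.5 in units of the baseline-adjusted SD), power from the noncentral t with schools minus 4 degrees of freedom and noncentrality 0.5 / √(4 × DE / N) is, at ICC 0.02 / 0.05 / 0.10:
- 6 schools of 42: 38% / 26% / 18%
- 12 schools of 21: 84% / 69% / 52%
- 18 schools of 14: 91% / 82% / 68%
- 30 schools of 8: 94% / 89% / 82%

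The 95% in section 2.4.2 is not reached in any of these, so the sample size and the minimum number of schools should be revisited at the same time. More schools help far more than more pupils per school.
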